### Outcome Measures

According to interventions already undertaken with distinctive dance forms [9,21,24-27], it is believed that the samba classes can generate positive results in both motor symptoms and non-motor symptoms. The expectation is that the activity will have a greater effect on the primary outcomes such as motor exploration and balance, and a minor effect on non-motor symptoms such as depression and fatigue. We also decided to include an assessment for sleep disorders, as this outcome is still not observed in dance studies. To maintain uniformity in the results of future studies, we chose the more popular assessment tools for each variables, as well as the number of outcomes. Table 1 lists the variables to be evaluated, as well as the instruments used to measure them.

### Ethical Approval

The project was approved by the Research Ethics Committee in Human Beings, University of Santa Catarina State under the protocol 1.268.353.

**Table 1 table1:** Variables and instruments used for assessment of the outcomes in individuals with PD.

Variables		Definition	Instruments
**Symptomatology**				
	General condition of the patient with PD	Light disability, Moderate disability, High disability	HY^a^-Degree of Disability Scale
	Evaluation of PD	Progression of the disease	UPDRS^b^	
**Motor/Non-motor Symptoms**				
	Balance	Restricted to the wheelchair; Needs during walking; Independent walking	BBS^c^
	Sleep quality	‒	PDSS^d^
	Depressive symptoms	Minimal, mild, moderate, severe	BDI^e^
	Fatigue	‒	FSS^f^
	Quality of life	‒	PDQ-39^g^

^a^HY: Hoehn and Yahr.

^b^Unified Parkinson's Disease Rating Scale.

^c^BBS: Berg Balance Scale.

^d^PDSS: Parkinson’s Disease Sleep Scale.

^e^BDI: Beck Depression Inventory.

^f^FSS: Fatigue Severity Scale.

^g^PDQ-39: Parkinson’s Disease Questionnaire.

### Data Collection

#### Experimental Group

The classes will be held at the CCR while participants are taking their medication. They will be invited to participate in the study voluntarily and to take part in the dance classes. The potential participants will be provided with an explanation of the study procedures (assessment prior to data collection, dance classes, and assessment after data collection) and the importance of attending the classes for health benefits. After the participants sign the informed consent forms, we will start collecting data. The questionnaires will be filled out before the dance intervention in a quiet place to facilitate subjects’ understanding of the questions, during a 2-week period preceding the application of the protocol. After the initial assessment, the dance classes will start twice a week and last 1 hour each time, according to the study protocol. At the end of the 12-week course, a second assessment will be held, in the same manner as the first one.

#### Control Group

The data collection for the control group will be held simultaneously to the intervention group of the period. The researcher will schedule a visit to the patient’s home or other preferred place, where they will clarify the goals of the study, emphasize the importance of keeping to normal daily activities, and request that the patient avoids starting a physical activity during these 12 weeks. The subjects in the control group will also be advised that not performing physical activity for 12 weeks is against the guidance for prevention of disease and maintenance of health, and therefore, it is only a guideline.

The participants in the control group will be invited to monthly lectures that address the maintenance of health, prevention of falls, and psychological care. They will be asked, in person, about their general health and performance of daily activities. During the interview after the 12 weeks of data collection, any subjects who state that they have started a regular physical activity of any type will be excluded from the control group. At the end of the study, all participants (control and intervention) will receive a booklet stating, in a clear and objective way, the main results for both the group and individually (including the activities started during the period and the option to be excluded from the databank). Since the dance classes will continue after the end of the study, all participants will be invited to take part in them.

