## Methods

### Study Type

This clinical non-randomized study comprises 12 weeks of intervention and monitoring of a control group (Figure 1).

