**Figure 1 figure1:**
[figure not shown]
Flowchart showing the process of participant selection and steps in the study protocol.

Inclusion criteria consist of individuals of both sexes; aged ≥50 years; with a clinical diagnosis of PD, according to the criteria of the London Brain Bank [22]; on stable doses of medication; who attend one or two times weekly, a physiotherapy section and who have not participated in any dance classes for at least 3 months. Exclusion criteria consist of people who are taking part in combined practice of any physical activity program and/or exercise; fail to complete all stages of the study (intervention); are decompensated clinically; do not meet the cut-off points on the Mini-Mental State Examination, in accordance with the criteria established by Bertolucci et al [23] for the Brazilian population (13=illiterate, 18=medium level of education, 26=high school); and with physical disability affecting daily or social life activities, due to a condition other than PD.

In order to avoid confusion bias before the intervention, participants will be excluded from either of the groups, if they have participated in systematic physical activity, for at least 3 months prior to the start of the study.

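### Participants are removed after group assignment for not completing the study or, by a 12-week check described only for controls, for starting exercise; this can bias the comparison, probably towards samba

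*Protocol article*

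**What the plan says.** Two rules in the protocol article act on events that happen after a participant has joined a group.

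- **Non-completion.** The exclusion criteria under Participants (below Figure 1) include people who "fail to complete all stages of the study (intervention").
- **Starting exercise.** Under Control Group, at the interview after the 12 weeks, "any subjects who state that they have started a regular physical activity of any type will be excluded from the control group".

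Three other statements bear on how these rules work.

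- The activity rule that names both groups looks back before the study: "participants will be excluded from either of the groups, if they have participated in systematic physical activity, for at least 3 months prior". A further exclusion, not limited to one group, covers people in "combined practice of any physical activity program and/or exercise".
- Controls are approached with a "request that the patient avoids starting a physical activity during these 12 weeks". They are also told that "not performing physical activity for 12 weeks is against the guidance for prevention of disease and maintenance of health", and the text concludes that "therefore, it is only a guideline".
- Study Type states the design: "This clinical non-randomized study comprises 12 weeks of intervention". Statistical Analysis and Sample Size plans a two-way repeated-measures ANOVA on 25 analysable participants per group, raised to 30 for a loss of about 20%. Nothing there returns removed participants to the comparison.

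**The concern.** An eligibility criterion can be checked before a participant enters a group. Neither rule can be: completion is known only at the end, and new activity is established at the 12-week interview. Both therefore select the analysed groups on behaviour during follow-up, and that behaviour is plausibly related to motor outcome. Dancers who stop may be those who are ill, falling or not improving. Controls who take up exercise may gain motor function.

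If so, the dance group loses some of its worst changes and the control group some of its best. A difference could then appear without any samba effect. The result would also describe compliant completers rather than people offered the programme, although the article's Conclusions present compliance as an advantage of dance. The control rule is avoidable in a further sense: it is applied while the participant is still in contact, so obtainable outcome data are discarded.

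**Working it through.** **1. Timing and reach of each rule**

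| Rule | When it can be known | Group named |
|---|---|---|
| Prior systematic activity (Participants) | before the start | either group |
| Concurrent exercise (Participants) | at entry; no follow-up check described | not limited |
| Not completing all stages (Participants) | during or after follow-up | not stated, apart from the word intervention in brackets |
| Started regular activity (Control Group) | 12-week interview | controls only |

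The last two act after assignment. An explicit 12-week activity check with removal is described only for controls; the Experimental Group section describes none.

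**2. The plan's own loss figure**

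25 × 1.2 = 30 per group reproduces the stated enrolment. This is a general allowance for loss. The article does not say how much of it these two rules would cause, so any removal rate below is an assumption. Of 30 per group, 10% is 3 participants and 20% is 6.

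**3. Shift from selective removal**

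Let a fraction q be removed from one end of a latent score that correlates r with the change score. The mean change of those kept then moves, in SD units of change, by

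r × φ(z_q) / (1 − q),

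where z_q is the standard normal quantile at q and φ the normal density.

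- q = 0.10: 0.039, 0.058 and 0.097 for r = 0.2, 0.3 and 0.5.
- q = 0.20: 0.070, 0.105 and 0.175 for the same r.

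If the lowest dancers and the highest controls are removed, the two shifts add.

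**4. Simulation with no true effect**

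There were 30 per group, 20,000 runs and a two-sided 5% t test on change. With two groups and two time points, this test is equivalent to the group-by-time test in the planned ANOVA. Removal was equal in both groups, in the direction unfavourable to a fair comparison.

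| Removed per group | r | Formula (SD) | Simulated difference (SD) | Type I error |
|---|---|---|---|---|
| 10% | 0.2 | 0.078 | 0.074 | 0.059 |
| 10% | 0.3 | 0.117 | 0.114 | 0.072 |
| 10% | 0.5 | 0.195 | 0.186 | 0.114 |
| 20% | 0.2 | 0.140 | 0.139 | 0.078 |
| 20% | 0.3 | 0.210 | 0.205 | 0.112 |
| 20% | 0.5 | 0.350 | 0.336 | 0.234 |

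With selective removal of 20% in one group only, the simulated difference is about 0.07 to 0.17 SD and the type I error 0.056 to 0.100.

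**5. When the bias is small or absent**

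- If removal is unrelated to change (r = 0), the formula gives 0.
- If both groups lose their worst participants at equal rates, the simulated difference lies between −0.002 and 0.001 SD and the type I error between 0.046 and 0.062.
- If 20% of dancers and 10% of controls are removed in offsetting directions at r = 0.3, the net shift is 0.105 − 0.058 = 0.047, or about 0.05 SD.

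**6. A direct look at the control rule**

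If a fraction q of controls start exercise and each gains g SD from it, removing them lowers the control mean change by q × g. With assumed q of 10-20% and g of 0.2-0.6 SD, the range is 0.10 × 0.2 = 0.02 to 0.20 × 0.6 = 0.12 SD.

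**The case against.** **Direction.** A reader might infer that the removals are shown to favour samba. The documents do not support that. They do not say why dancers stop or why controls begin exercise. Twice-weekly evening classes can be missed for reasons unrelated to symptoms. Controls are invited to lectures on health and fall prevention, and those who are worsening may be the ones who respond. This stands: the direction is expected, not demonstrated.

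**Asymmetry.** A reader might also infer that a dancer who adds outside exercise is certainly kept. The concurrent-exercise exclusion is not limited to one group, and it sits in the same list as an on-study criterion, so it could be read as covering dancers too. The booklet described under Control Group, which goes to both groups, mentions activities started during the period, so new activity may be recorded in both. What is secure is narrower: the explicit 12-week check and removal is described for controls alone.

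**Non-completion.** Completing all stages may include the assessments, and no attendance threshold is given. Some of those removed may simply lack a second assessment, which is ordinary missing data. This limits the claim about size. It does not justify listing non-completion as an exclusion.

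**The advisory wording.** Calling the request to controls a guideline creates no bias in itself. It does make it foreseeable that some controls will become active and be dropped.

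**Design.** Excluding active controls serves, crudely, the stated comparison with a group without intervention. Without randomisation, analysis by original group does not by itself make the groups comparable. Both points are fair. Neither makes it sound to add selection during follow-up to the confounding already present.

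**Conclusion.** The concern holds in this form: the protocol fixes two removals that act after assignment and select the analysed groups on behaviour plausibly linked to outcome. They can bias the comparison, probably in favour of samba, and they restrict the result to compliant completers. Nothing else in the article undoes them.

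The size cannot be derived from the documents. The range of about 0.07-0.34 SD, with a type I error of about 6-23%, rests on three assumptions: 10-20% removed per group, removal in the unfavourable direction in both groups, and a correlation of 0.2-0.5 with change. It would be a misreading to take the upper end as the study's expected error rate, or to treat the plan's general 20% loss allowance as outcome-related removal. The distortion is near zero if selection is unrelated to outcome or the removals offset, and it could reverse if controls exercise because they are getting worse. An unknown bias of uncertain sign is still reason to change the rules, because the remedy is simple.

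**What to change.** - Delete non-completion of all stages from the exclusion criteria under Participants.
- Delete the removal of controls who start activity under Control Group.
- Invite every enrolled participant to the 12-week assessment already planned, whatever their attendance or activity. State that the primary analysis includes all those with outcome data, in their original group.
- Ask about attendance and new physical activity with the same question in both groups.
- Keep the completer or compliant analysis, with one activity rule for both groups, as a labelled sensitivity analysis.

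The cost is protocol wording and the work of calling back non-attenders. No additional participants are needed, since up to 60 rather than the planned 50 would be analysed. The downside is some dilution of the estimated effect. Confounding from non-random assignment remains and is not addressed by this change.

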### Statistical Analysis and Sample Size

Sample size was based on primary outcomes and calculation performed with the G*Power 3.1.9.2 software [28], assuming a moderate effect of Brazilian samba on motor signals (UPDRS III), according to Cohen [29] with 0.447 effect size. We chose a more cautious effect size because there is still no evidence of Brazilian samba in DP rehabilitation. However, due to the effects already found in similar interventions (ref=-0.62/-0.55) [30] as described in the meta-analysis by Lutzke et al, a significant effect is expected regarding to motor symptoms. We used alpha=.05 and power of 0.9, applied in two groups (experimental group and control group) analyzing the results through a two-way analysis of variance (ANOVA) with repeated measures and Sidak post-hoc comparison test for a comparative analysis into and between groups. Significance level will be set at 5%. Anticipating 25 individuals in each group, but foreseeing a sample loss of around 20% [31,32], we have chosen to include 30 individuals per group, ending with a total of 60 subjects.

After the intervention, the data will be transferred to SPSS v. 20.0. First, descriptive statistics will be performed (mean, standard deviation, and percentage). Two-way ANOVA with repeated measures and Sidak post-hoc comparison test will be used for a comparative analysis of the results of the control group with the experimental group and of the within-group changes between pre- and postintervention period. Significance level will be set at 5%.

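### Controls who report new regular activity at 12 weeks are removed after baseline, with no clearly written equivalent for dancers, so the samba contrast can be biased

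*Protocol article*

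**What the plan says.** The rule is in the Protocol article, Methods, Data Collection, Control Group. The researcher is to "request that the patient avoids starting a physical activity during these 12 weeks", and controls are told that abstaining is "against the guidance for prevention of disease and maintenance of health, and therefore, it is only a guideline". At the interview after 12 weeks, "any subjects who state that they have started a regular physical activity of any type will be excluded from the control group".

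The parallel Experimental Group section covers consent, a baseline assessment, the classes and a second assessment. It does not mention other activity taken up during the 12 weeks.

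Three other statements bear on the dancers:
- The exclusion list under Participants bars "people who are taking part in combined practice of any physical activity program and/or exercise" and names no arm. The next item excludes people who do not complete the study stages, which can only apply after enrolment.
- Also under Participants, "participants will be excluded from either of the groups, if they have participated in systematic physical activity". This rule covers both arms, but only the three months before the start.
- Under Control Group, participants in both arms receive a results booklet, "including the activities started during the period and the option to be excluded from the databank".

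The sample size section reads "Anticipating 25 individuals in each group, but foreseeing a sample loss of around 20" per cent, and sets 30 per group.

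**The concern.** The objective is to compare samba with a group without intervention. Removing active controls looks like a way to keep that comparator clean, but it selects on something that happens after baseline. People who take up exercise within 12 weeks may be fitter or more motivated, or may benefit from the exercise itself. In either case, taking them out of the control arm lowers its mean change. If comparable dancers stay in, their change counts as samba. The motor outcomes (UPDRS III, Berg Balance Scale) are exposed as well as the non-motor ones.

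Removals are foreseeable, because controls are told that the request is advisory and contrary to health guidance. The study is non-randomised, so this selection would add to whatever confounding is already present.

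**Working it through.** **Loss allowance (from the article).** 25 × 1.2 = 30 per arm, so the allowance is 30 − 25 = 5 per arm. Five removals would use all of it in the control arm before any dropout. If dropouts have already used it, 3 or 5 further removals leave 22 or 20 controls against 25 dancers:
- √(1/25 + 1/22) / √(2/25) = 1.034, a standard error 3.4% wider.
- √(1/25 + 1/20) / √(2/25) = 1.061, a standard error 6.1% wider.

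**Bias with equal uptake (inputs assumed).** The article gives neither uptake nor the difference between starters and the rest. With two groups and two time points, the group-by-time test equals a two-sample t-test on change scores. Assume no samba effect, 25 per arm, k starters in each arm, starters' mean change g SD better than the rest, and SD 1 within each subgroup. Set the non-starters' mean at 0.
- Dancers, all kept: mean = (k/25) × g.
- Controls after removal: mean = 0.
- Shift in the contrast = (k/25) × g.

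The last column comes from simulation (200,000 runs, two-sided 5% test; nominal rate in one direction 2.5%).

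| Starters per arm | g (SD) | Shift (SD) | False significance favouring samba |
|---|---|---|---|
| 3 (12%) | 0.2 | 0.024 | 3.0% |
| 3 (12%) | 0.5 | 0.060 | 3.8% |
| 3 (12%) | 0.8 | 0.096 | 4.7% |
| 5 (20%) | 0.2 | 0.040 | 3.3% |
| 5 (20%) | 0.5 | 0.100 | 4.9% |
| 5 (20%) | 0.8 | 0.160 | 6.7% |

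At g = 0 the shift is 0 and the rate is 2.5%. At g = −0.5 with 5 starters the shift is −0.100, against samba. Keeping everyone in both arms gives a shift of 0 and 2.0% to 2.4%.

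Larger assumptions give larger figures. With 30 per arm, 10% to 30% uptake and a total gap of 1.0 SD (0.5 from the activity, 0.5 from prognosis), the shift is about 0.10 to 0.30 SD and the two-sided test rejects about 6% to 17% of the time.

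**Bias with unequal uptake (inputs assumed).** Split g into s, the better change starters would have had anyway, and a, the activity's own effect. Let uptake be p in controls and q in dancers, and assume the arms otherwise have the same prognosis. Measured against a comparison with no new activity in either arm:
- Removing control starters only: shift = p × s + q × a.
- Keeping everyone: shift = (q − p) × a.

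With p = 20% and q = 0:
- s = 0, a = 0.5: removal gives 0; keeping everyone gives −0.20 × 0.5 = −0.10 SD.
- s = 0.5, a = 0: removal gives 0.20 × 0.5 = +0.10 SD; keeping everyone gives 0.

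**The case against.** The strongest objection is that the one-sidedness is not established. The exclusion for combined practice names no arm, can be read as activity alongside the study, and sits beside a criterion that only works after enrolment. The booklet for both arms suggests that dancers' new activities are recorded too. A condensed article may also omit the dancers' interview script. This stands in part. A reader might infer that dancers are never asked about new activity and never removed for it, but the article does not support that. It does support a narrower statement: an explicit 12-week removal is written for controls, and none is clearly written for dancers. If the general exclusion already covered new activity in both arms, the separate control rule would be redundant.

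A second objection is that equal uptake is doubtful, because only controls are asked to refrain and dancers already attend two classes a week. This also stands. As shown above, keeping everyone gives exactly zero shift only at equal uptake. If the gap were purely the activity's own effect and few dancers took up activity, removal could be the less biased rule for a comparator with no new activity. That does not rescue the rule where starters differ in prognosis, since removal then distorts the control arm even when no dancer starts anything.

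A third objection is that the planned loss may already be meant to cover such exclusions. The wording is not limited to dropouts, so this is possible. Removals and dropouts would still share the same 5 places.

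**Conclusion.** The concern holds in a limited form. As written, the plan removes controls on a post-baseline, self-reported behaviour, and the handling of dancers who do the same is unclear. That can bias the contrast.

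A reader might go further and conclude that the rule inflates the samba effect. The documents do not support this, because they give neither uptake nor the direction in which starters differ. A tilt towards samba is plausible if starters are fitter or benefit from the activity. There is no bias if starters do not differ, and the sign reverses if controls take up activity because they are worsening.

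Under equal uptake of 12% to 20% and gaps of 0.2 to 0.8 SD, the effect is modest. Keeping everyone does not guarantee an exactly unbiased answer when uptake differs, but it avoids selecting controls on what they did after entry. That is reason enough to change the analysis set, even though the size is uncertain.

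**What to change.** - Ask the same question about newly started activity in both arms at 12 weeks.
- Drop the control-only removal. Keep all enrolled participants with 12-week data in the primary analysis, regardless of new activity.
- Exclude newly active participants only in a sensitivity analysis, applied identically to both arms.

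The request that controls avoid starting activity may stay; removing it would change the comparator and is not needed to repair this defect. The exclusion of participants who do not complete the intervention is a separate post-entry selection that this change does not address.

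The cost is a small revision of the interview script, one activity question for dancers and an ethics notification. The downside is that active controls kept in the analysis may slightly narrow the contrast.
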